**Objective:**

We aimed to collect and analyze data on the major clinical characteristics of patients with stroke receiving KM treatment and investigate the effectiveness and safety of KM in the Korean population.

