## Methods

### Study Design

The RoS-KoMH is a voluntary multicenter, prospective, observational disease registry attempting to explore the demographics, clinical features, treatment status, therapeutic outcomes, and safety of patients with stroke in Korea who are treated using KM in KM hospitals and establish clinical evidence to improve treatment outcomes in the future. A flowchart of the study process is shown in Figure 1. This study will be conducted by the Kyung Hee University Korean Medicine Hospital (KH) located in Seoul, Dongguk University Ilsan Korean Medicine Hospital (DG) located in Gyeonggi-do, Wonkwang University Gwangju Medical Center (WK) located in Gwangju, and Pusan National University Korean Medicine Hospital (PS) located in Gyeongsangnam-do. The protocol was registered with the Clinical Research Information Service (KCT0008494) on June 2, 2023, and reported in accordance with the SPIRIT (Standard Protocol Items: Recommendations for Interventional Trials) checklist (Multimedia Appendix 1).

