### Study Participants

#### Inclusion Criteria

The inclusion criteria for the study are as follows:

Men and women aged 19 years or older.Patients diagnosed with a stroke (including ischemic stroke, hemorrhagic stroke, or subarachnoid hemorrhage; 10th revision of the International Classification of Diseases codes I60-I63) based on the results of clinical examination and radiologic examination and receiving treatment at an outpatient clinic or an inpatient ward of a KM hospital.Patients who understood the purpose and intent of the study and voluntarily agreed to participate through written consent from the patient or their caregiver or representative.

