### Number of Participants

The purpose of this study was not to statistically verify the intervention effect of KM treatment for stroke but to explore the demographics, clinical aspects, treatment status, and therapeutic efficacy and safety of KM for patients with stroke patients in Korea and to provide clinical evidence to improve the therapeutic effect of KM treatment in the future.

Accordingly, a total of 500 sets of clinical information on patients with stroke will be collected based on the opinions of the researchers, considering the financial resources, the environment in which the study is conducted, and the appropriate number needed to achieve the goal. One set was defined as a stroke patient for whom information was collected at the time of the first outpatient visit or admission, and additional information was collected at any point (4, 8, or 12 weeks) after the first outpatient visit or admission. For example, if information was collected for a single patient once upon admission, once in the fourth week of hospitalization, and once again in the eighth week of hospitalization, 2 sets of information would be considered collected.

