### Data Analysis

Statistical analyses will be performed with SPSS version 21.0 (IBM Corporation) by our biostatisticians at the RoS-KoMH. Descriptive statistics will be used to analyze the data, and all measures will be presented as means (SDs) for continuous variables and n (%) for dichotomous variables. For variables assessed more than once, the amount or rate of change from baseline to follow-up will be calculated.

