## Discussion

With increasing interest in the effects, benefits, and adverse effects of various treatments, well-designed, large-scale registries related to the long-term clinical outcomes of patients with stroke should be prioritized by clinicians and researchers [19]. Here, we describe the rationale and design of a prospective, multicenter, registry-based observational study investigating the clinical characteristics, KM stroke management, and outcomes of patients with acute stroke in a real-world setting in Korea. This study is expected to provide comprehensive real-world data on the demographic characteristics, treatment patterns, clinical outcomes, and safety of KM in stroke care across multiple institutions in Korea.

Considering that the current evidence-based guidelines for acute treatment and rehabilitation for stroke still have limitations despite several advances over the last few decades, the need for more effective and safer treatments to improve the prognosis of patients with stroke is constantly increasing [16]. Clinical KM studies on stroke have shown the efficacy of combined herbal treatment for acute ischemic stroke [20], the secondary prevention effect of herbal extracts on ischemic stroke [21,22], the benefits of acupuncture for stroke rehabilitation [23], the prevention effect of acupuncture [24], the improvement of dysphagia following acupuncture [25], the effect of pharmacopuncture on poststroke shoulder pain [26], and the effect of herbal treatment on chronic subdural hemorrhage [27]. The safety of KM treatment for stroke has also been reported, including the safety of combining warfarin with herbal medicine [28], the safety of liver and kidney function with the coadministration of western medicine and herbal medicine in patients with stroke [29], and the safety of combining acupuncture with warfarin [30] and novel oral anticoagulants in patients with stroke [31]. Most of these were retrospective cohort studies, cross-sectional studies, or systematic reviews that evaluated specific treatments or effects, which are common research methods used to generate evidence for KM and have been criticized for the quality of evidence on efficacy and safety. Therefore, it is necessary to improve the quality of evidence for the use of KM for patients with stroke.

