Some characteristics of KM have made it difficult to build high-level evidence for it. In other words, KM is an empirical medicine that has accumulated over a long period, and it is difficult to standardize and objectively evaluate treatment because it provides customized treatment according to patient characteristics and requires a long treatment period and long-term follow-up. One way to supplement these points is to collect and use large-scale data [32]. Large-scale data use studies on KM in Korea are rare. In Taiwan, 99% of people are enrolled in national health insurance, and most traditional medicine treatments, including traditional Chinese medicine, are covered by national health insurance and used to generate evidence and improve treatment quality [33]. However, in the case of health insurance databases in Korea, KM is limited in that data cannot be obtained because major treatments such as herbal medicine (with some exceptions), pharmacopuncture, and bee venom acupuncture are not covered by national health insurance. Therefore, we designed the RoS-KoMH to compensate for these limitations by collecting information that can be obtained when treating patients with stroke patients at KM hospitals that actually treat stroke.

The RoS-KoMH protocol has some limitations. Although the RoS-KoMH registry collects longitudinal and multidimensional data, multivariate analyses, such as regression modeling or adjustment for potential confounders, have not yet been applied, which may limit causal inference regarding treatment outcomes given the variability in patient comorbidities and interventions. In addition, since the RoS-KoMH is a real-world, hospital-based, observational registry, it relies on voluntary participation to reflect the natural flow of patients receiving KM treatment for stroke in a routine clinical setting, which may lead to selection bias. The results of this study will provide evidence on the efficacy and safety of KM treatment for stroke to facilitate and standardize the optimization of individualized interventions for stroke prevention and treatment in Korea. Therefore, it is suggested that a registry study focusing on KM treatment be conducted using a stratified or consecutive sampling design as a follow-up to this study.

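### The only analysis stated, descriptive change from baseline in one KM-treated group with no limit on time since stroke onset, cannot support the evidence on effectiveness and efficacy that the article announces

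*Protocol article*

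**What the plan says.** **Aim and announced conclusions.** The abstract's Objective is to "investigate the effectiveness and safety of KM in the Korean population". The abstract's Conclusions list treatment effectiveness among the things on which high-quality evidence will be provided. The Discussion says: "The results of this study will provide evidence on the efficacy and safety of KM treatment for stroke".

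**Analysis.** Under Data Analysis, "Descriptive statistics will be used to analyze the data", with means and SDs or counts and percentages. For repeated measures: "For variables assessed more than once, the amount or rate of change from baseline to follow-up will be calculated". No comparator, strata or adjustment is named.

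**Population.** Study Design describes patients "who are treated using KM in KM hospitals". Inclusion Criteria require a stroke diagnosis "based on the results of clinical examination and radiologic examination and receiving treatment at an outpatient clinic or an inpatient ward of a KM hospital". Neither the inclusion nor the exclusion criteria limit time since onset. The 7-day period under Recruitment of Participants is counted from the KM hospital visit or admission. The Discussion nevertheless speaks of "outcomes of patients with acute stroke in a real-world setting in Korea".

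**Qualifications.** Number of Participants states: "The purpose of this study was not to statistically verify the intervention effect of KM treatment for stroke". The limitations paragraph of the Discussion says that confounder adjustment has not so far been applied and that this may limit causal inference.

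**The concern.** The claim and the analysis do not match. A mean change from baseline in patients who all receive KM mixes at least three things: any effect of KM, recovery that would have happened anyway, and the effect of physical, occupational, speech and swallowing therapy and Western drugs given over the same weeks. Nothing in the stated analysis separates them.

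The open onset window adds to this. Eligibility allows a patient days after a stroke and a patient years after one. If these groups are expected to recover at different rates, an overall mean depends on their proportions and may describe neither group well. Calling the patients acute hides that mix.

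At stake is whether the registry's main outcome tables can carry the conclusion drawn from them. A favourable mean change could be read as evidence for KM when the design cannot show it.

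**Working it through.** The article gives no recovery figures, no distribution of time since onset, and no power calculation, so there is no figure of the plan to reproduce. The check is a comparison of its sections, followed by an illustration on assumed values.

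**1. Sections side by side**

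| Question | What the article gives | Where |
|---|---|---|
| What is to be learned? | Effectiveness or efficacy, and safety | Abstract (Objective, Conclusions); Discussion |
| Compared with whom? | Nobody; all are treated with KM | Study Design; Inclusion Criteria |
| How long after stroke? | No limit | Inclusion and Exclusion Criteria |
| What else is given? | Rehabilitation and Western drugs, recorded at each visit or daily | Rehabilitation Therapies; Concomitant Treatment |
| What is computed? | Descriptive change from baseline | Data Analysis |
| Could timing be used? | Yes; onset date and stroke type are collected | Baseline Data; Table 1 |

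The first row needs a contrast between KM and its absence. No later row supplies one.

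**2. Dependence on case mix (assumed inputs)**

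Let the KM effect be zero, and let early and late patients gain 20 and 2 modified Barthel points without it. Then overall mean change = p × 20 + (1 − p) × 2, where p is the share of early patients.

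- p = 0.3: 0.3 × 20 + 0.7 × 2 = 7.4 points
- p = 0.7: 0.7 × 20 + 0.3 × 2 = 14.6 points

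The apparent improvement about doubles with no change in treatment effect.

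**3. Would a larger sample help? (assumed inputs)**

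Let a share s of patients recover spontaneously by r SDs of the change score, again with zero KM effect. Mean change = s × r. For s from 0.25 to 1 and r from 0.2 to 0.8, this runs from 0.25 × 0.2 = 0.05 SD to 1 × 0.8 = 0.80 SD.

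The target is 500 sets. A set is a baseline plus one follow-up at 4, 8 or 12 weeks, so a patient can supply up to three. The number of patients therefore lies between 500/3, rounded up to 167, and 500. For s = r = 0.5 the mean is 0.25 SD, and the lower 95% limit is 0.25 − 1.96/√n:

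- n = 167: 0.25 − 0.15 = 0.10 SD
- n = 500: 0.25 − 0.09 = 0.16 SD

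Under these inputs a treatment with no effect shows an improvement whose interval excludes zero, and more patients only make it look firmer. With a small share and slow recovery the interval would include zero, so the result depends on inputs the article does not give.

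**The case against.** The strongest reply is that this is a registry and says so. The lack of a comparator and the broad eligibility suit a descriptive purpose. Number of Participants disclaims statistical verification of the effect, and the Discussion admits that causal inference may be limited, given variation in comorbidities and interventions. Interventions may well include rehabilitation and drugs, and the wording leaves later adjustment open.

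Much of this stands. Two stronger readings are tempting, and the document supports neither:

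- **That recovery and rehabilitation effects will be reported as a KM effect.** This is a prediction. Data Analysis promises calculated changes and attributes them to nothing, and no data had been analysed at the time of writing.
- **That the analysis is unstratified.** The article names no strata but excludes none. It is a condensed account, and a fuller analysis plan may exist. Nor can onset date and rehabilitation be called ignored, since all measures are to be presented.

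The reply does not remove the mismatch. The sentence that disclaims verification goes on to list therapeutic efficacy among the things to explore. The limitations paragraph names comorbidities, interventions and voluntary participation, but not natural recovery, time since onset or the missing comparator, and it then still announces efficacy evidence. Its proposed remedy, stratified or consecutive sampling in a later study, concerns selection and not attribution.

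**Conclusion.** The point holds as a mismatch between what is claimed and what is analysed. The stated descriptive change cannot support a conclusion on effectiveness or efficacy, and the authors' own caveats disclose this only in part. Separately, the acute-stroke label in the Discussion does not agree with the eligibility criteria.

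The direction follows if untreated recovery is positive on average: change from baseline then overstates what KM contributed. The size cannot be derived. The Barthel and SD figures above rest on assumed inputs and only show that the mean can move substantially with case mix while the KM effect stays at zero. How many early patients the registry actually enrols is not known from the article.

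**What to change.** 1. **Data Analysis.** Present change from baseline by time since onset at enrolment, in bands fixed before the data are examined, and by stroke type and inpatient or outpatient status, with 95% confidence intervals. Describe rehabilitation exposure alongside. Onset date, stroke type and rehabilitation are already collected, and care setting follows from the visit structure.
2. **Objective, Conclusions and Discussion.** Replace the effectiveness and efficacy wording with clinical course under KM care, and state that change cannot be attributed to KM. Name natural recovery, time since onset and the missing comparator among the limitations.
3. **Discussion and Inclusion Criteria.** Reconcile the acute-stroke description with the eligible population.

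A covariate-adjusted model is optional. It could describe who changes more, but without a comparator it would not isolate a KM effect, so the rewording is needed either way.

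The cost is more modest conclusions, some extra tables and less precision in smaller strata. No new data are needed. The change is timely: the article reports that no analysis had been done as of September 25, 2024, and recruitment is scheduled to run to December 31, 2026.

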### Ethical Considerations

The study protocol was approved by the Institutional Review Board of Kyung Hee University Korean Medicine Hospital (KOMCIRB 2021-06-003-001, approved on August 13, 2021), Dongguk University Ilsan Korean Medicine Hospital (DUIOH 2021-10-008-002, approved on August 30, 2022), Wonkwang University Gwangju Medical Center (WKIRB 2021/7-2, approved on September 29, 2021), and Pusan National University Korean Medicine Hospital (PNUKHIRB 2021-11-003-001, approved on December 22, 2021). This study is conducted in accordance with the principles of the Declaration of Helsinki. Participants who wish to participate will receive an explanation of the consent form and must provide written consent of their own free will. All data from participants will be simultaneously recorded in an eCRF with an identification code rather than the participant’s name to protect personal information.

## Results

The study was funded by the Ministry of Health and Welfare, Republic of Korea (grant RS-2020-KH088006) on August 19, 2020. Recruitment for the registry commenced on November 3, 2021, and is scheduled to end on December 31, 2026. As of September 25, 2024, a total of 410 sets have been collected: 171 from KH, 88 from DG, 125 from WK, and 26 from PS. At this point, no data analysis has been conducted.

## Discussion

With increasing interest in the effects, benefits, and adverse effects of various treatments, well-designed, large-scale registries related to the long-term clinical outcomes of patients with stroke should be prioritized by clinicians and researchers [19]. Here, we describe the rationale and design of a prospective, multicenter, registry-based observational study investigating the clinical characteristics, KM stroke management, and outcomes of patients with acute stroke in a real-world setting in Korea. This study is expected to provide comprehensive real-world data on the demographic characteristics, treatment patterns, clinical outcomes, and safety of KM in stroke care across multiple institutions in Korea.

Considering that the current evidence-based guidelines for acute treatment and rehabilitation for stroke still have limitations despite several advances over the last few decades, the need for more effective and safer treatments to improve the prognosis of patients with stroke is constantly increasing [16]. Clinical KM studies on stroke have shown the efficacy of combined herbal treatment for acute ischemic stroke [20], the secondary prevention effect of herbal extracts on ischemic stroke [21,22], the benefits of acupuncture for stroke rehabilitation [23], the prevention effect of acupuncture [24], the improvement of dysphagia following acupuncture [25], the effect of pharmacopuncture on poststroke shoulder pain [26], and the effect of herbal treatment on chronic subdural hemorrhage [27]. The safety of KM treatment for stroke has also been reported, including the safety of combining warfarin with herbal medicine [28], the safety of liver and kidney function with the coadministration of western medicine and herbal medicine in patients with stroke [29], and the safety of combining acupuncture with warfarin [30] and novel oral anticoagulants in patients with stroke [31]. Most of these were retrospective cohort studies, cross-sectional studies, or systematic reviews that evaluated specific treatments or effects, which are common research methods used to generate evidence for KM and have been criticized for the quality of evidence on efficacy and safety. Therefore, it is necessary to improve the quality of evidence for the use of KM for patients with stroke.

Some characteristics of KM have made it difficult to build high-level evidence for it. In other words, KM is an empirical medicine that has accumulated over a long period, and it is difficult to standardize and objectively evaluate treatment because it provides customized treatment according to patient characteristics and requires a long treatment period and long-term follow-up. One way to supplement these points is to collect and use large-scale data [32]. Large-scale data use studies on KM in Korea are rare. In Taiwan, 99% of people are enrolled in national health insurance, and most traditional medicine treatments, including traditional Chinese medicine, are covered by national health insurance and used to generate evidence and improve treatment quality [33]. However, in the case of health insurance databases in Korea, KM is limited in that data cannot be obtained because major treatments such as herbal medicine (with some exceptions), pharmacopuncture, and bee venom acupuncture are not covered by national health insurance. Therefore, we designed the RoS-KoMH to compensate for these limitations by collecting information that can be obtained when treating patients with stroke patients at KM hospitals that actually treat stroke.

The RoS-KoMH protocol has some limitations. Although the RoS-KoMH registry collects longitudinal and multidimensional data, multivariate analyses, such as regression modeling or adjustment for potential confounders, have not yet been applied, which may limit causal inference regarding treatment outcomes given the variability in patient comorbidities and interventions. In addition, since the RoS-KoMH is a real-world, hospital-based, observational registry, it relies on voluntary participation to reflect the natural flow of patients receiving KM treatment for stroke in a routine clinical setting, which may lead to selection bias. The results of this study will provide evidence on the efficacy and safety of KM treatment for stroke to facilitate and standardize the optimization of individualized interventions for stroke prevention and treatment in Korea. Therefore, it is suggested that a registry study focusing on KM treatment be conducted using a stratified or consecutive sampling design as a follow-up to this study.

## Appendix

Multimedia Appendix 1 SPIRIT checklist.

## Abbreviations

eCRF: electronic case report form
KM: Korean medicine
RoS-KoMH: Registry of Stroke in Korean Medicine Hospital
SPIRIT: Standard Protocol Items: Recommendations for Interventional Trials
